### Sample size and power calculations

It is hypothesized that dietary supplementation with 4 g of myo-inositol daily for 12 months will reduce AAA growth by 40%, as evidenced by limiting increase in AAA volume from 8.1 ± 6.9 cm^3^ to 4.9 ± 6.9 cm^3^. Estimated outcomes for the control group are based on CT volume measured in a pilot cohort [53]. An effect size of 40% is based on the consideration of outcomes likely to be required for clinical efficacy. For example, if myo-inositol reduced annual increase in AAA size by 40%, the estimated time for an AAA initially measuring 40 mm to reach the commonly employed intervention level of 50 mm would be increased from 5 to ~ 7 years. Given that the annual mortality rate due to non-AAA-related causes is ~ 5% in patients with small AAAs, this reduction in growth could be expected to result in ~ 10% less patients requiring interventions over 5 years. This has significant potential social and economic benefit, with a possible cost saving of ~ $1 million per year [5, 6, 12]. On the basis of these estimated outcomes, 74 participants per group are required (80% power, α = 0.05) to detect the hypothesized reductions in AAA volume. Using data from a pilot cohort, it is estimated that this sample size will have a power of ~ 85% to detect a 40% reduction in orthogonal AAA diameter increase, assuming that the SD for the intervention group reduces in line with the mean. Allowing for a dropout rate of 10%, a total of 164 patients will be required. Sample sizes were calculated using G*Power 3.1 software.

### Data analysis

Analysis of primary and secondary endpoints will be based on intention to treat at the time of randomisation. All participants who meet the eligibility criteria, provide written informed consent and are enrolled in the study will be included in the primary analysis, regardless of adherence to supplement allocation. The efficiency of randomisation will be assessed by comparing the distribution of recognized determinants of AAA growth, such as initial AAA diameter, and background medication between the intervention and control groups.

The primary efficacy parameter is the between-group difference in mean AAA growth over 12 months as estimated by infrarenal aortic volume measured by CT. If there were to be no dropouts, the observed mean AAA volume increase over 12 months would be compared using a two-sample *t* test. However, it is expected that 10% of participants will drop out. AAA growth will therefore be analysed using a linear mixed model, specifying zero difference between treatment groups at baseline. The model will have two repeated dependent measurements. The fixed part of the model will contain the following covariates: time for CT measurement as a categorical variable, treatment, and interaction between treatment and CT time. The covariance part of the model will constitute a linear covariance matrix containing the following parameters: variance of CT measurements and covariance parameters. Without reference to the fixed part of the model, the goodness of fit of the assumed covariance model will be investigated. If necessary, the model will be extended with additional terms. The analysis will be performed using the PROC MIXED procedure in SAS software (SAS Institute, Cary, NC, USA), which is capable of fitting arbitrary linear covariance matrices. The main null hypothesis that will be tested is based on the treatment effect as estimated by this model at 12 months on CT measurements.

Secondary outcomes, including AAA diameter (CT and ultrasound), AAA PWS and PWRI, serum lipids, AAA biomarkers, RNA expression profile and SF-36 scores will be compared between the intervention and control groups using a linear mixed effect model similar to that described for the primary outcome. A number of additional analyses will also be performed, depending on the results of the primary analyses described above. These may include adjusted analyses using linear and logistic regression, such as where any important difference between the intervention and control groups are identified and Kaplan-Meier analyses to compare cardiovascular events and AAA repair rates.

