## Methods/design

### Study design

IMAGEN is a multi-centre, prospective, parallel-group, randomised, double-blind, placebo-controlled trial designed to assess if dietary supplementation with 2 g of myo-inositol twice daily for 12 months will reduce AAA growth. The trial will be conducted at four sites in Australia: The Royal Brisbane and Women’s Hospital, Brisbane; Gosford Vascular Services, Gosford; The Townsville Hospital, Townsville; and Mackay Base Hospital, Mackay. This trial protocol is reported according to the Standard Protocol Items: Recommendations for Interventional Trials (SPIRIT) (*see* Additional file 1). Only research personnel who are directly involved in the recruitment and data collection aspect of the study will have access to participants’ personal details. All case report forms (CRFs), source documentation and samples will be de-identified and coded with a study number, according to good clinical practice (GCP) guidelines.

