### Randomisation

The randomisation scheme will be generated from Stata code (StataCorp, College Station, TX, USA) and maintained by the central clinical trial pharmacist. Randomisation to myo-inositol or placebo will be stratified by study centre, presence of diabetes and aortic diameter (30–34, 35–39, 40–44, 45–49 and ≥ 50 mm) as measured on ultrasounds. Randomisation will be blocked in a 1:1 ratio (randomly to a maximum block size of 8). The central and site trial managers will be blinded to treatment allocation. Eligible and consenting participants will be allocated to inositol or placebo groups via a telephone call. Once an allocation number is obtained, the trial supplement will be dispensed by the local clinical trial pharmacist (after randomisation and at the 6-month time point). Allocation concealment will be achieved by using a central randomisation centre and employing identical packaging of intervention and placebo. Participants, investigators and outcome assessors will be blinded to treatment allocation. In the case of an emergency where breaking of the group allocation blinding is required, the local study centre clinical trial pharmacist will be contacted.

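### The primary mixed model leaves out the three stratification factors, which gives up some precision but causes no bias and no excess false positives

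*Protocol article*

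**What the plan says.** The Randomisation section of the protocol article states: "Randomisation to myo-inositol or placebo will be stratified by study centre, presence of diabetes and aortic diameter", with five diameter bands measured on ultrasound. Study design adds: "The trial will be conducted at four sites in Australia". Allocation uses blocks: "Randomisation will be blocked in a 1:1 ratio (randomly to a maximum block size of 8").

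The Data analysis section specifies a linear mixed model for the two CT volume measurements, "specifying zero difference between treatment groups at baseline". The fixed effects are given as a list: "The fixed part of the model will contain the following covariates", namely "time for CT measurement as a categorical variable, treatment, and interaction between treatment and CT time". The main null hypothesis is tied to the 12-month treatment effect from this model. The secondary outcomes are to be compared with a similar model.

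The same section counts initial AAA diameter among the recognised determinants of growth, and plans to compare it between the arms as a check on randomisation.

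Adjusted analyses appear only afterwards: "A number of additional analyses will also be performed, depending on the results of the primary analyses described above". These may include regression adjustment, "such as where any important difference between the intervention and control groups are identified".

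**The concern.** Stratified randomisation makes the arms more alike on the chosen factors, so the treatment difference varies less from trial to trial. A model that omits those factors does not see this. It leaves their share of the outcome variance in the residual and reports a standard error that is somewhat too large. The test then rejects less often than its nominal level, and power that the design has already paid for is not used.

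The protocol itself treats diameter as prognostic: it designs the allocation around diameter and then leaves it out of the model. Because the fixed part is an explicit list, this is a stated choice and not a detail left to a statistical analysis plan. At stake is precision in a trial planned at exactly 80% power.

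**Working it through.** **Inputs from the article.** Control growth 8.1 cm³, intervention 4.9 cm³, so the difference is 3.2; SD 6.9 in each arm; 74 per group; 80% power; α = 0.05 (taken as two-sided, which reproduces the figure). Strata: 4 centres × 2 diabetes levels × 5 diameter bands = 40. With 164 participants that is 164/40 = 4.1 per stratum.

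**Input not in the article.** R², the share of growth variance that the three factors explain beyond baseline volume. It is assumed at 0 to 0.20.

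**Step 1: the plan's own figure.** Noncentrality = 3.2 / (6.9 × √(2/74)) = 2.82 on 146 df. The noncentral t distribution gives power 80.0%, so 74 per group reproduces for the unadjusted comparison.

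**Step 2: power with adjustment.** The residual SD becomes 6.9 × √(1 − R²), with 8 df spent (3 centre, 1 diabetes, 4 diameter bands).

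| Assumed R² | Residual SD | Power at 74 per group |
|---|---|---|
| 0 | 6.90 | 80.0% |
| 0.04 | 6.76 | 81.6% |
| 0.05 | 6.73 | 82.0% |
| 0.10 | 6.55 | 84.0% |
| 0.20 | 6.17 | 87.9% |

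Entering diameter as continuous spends 5 df instead of 8 and changes these figures by about 0.01 percentage point.

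**Step 3: what the baseline constraint already captures.** Setting the baseline difference to zero effectively conditions on baseline CT volume, which tracks diameter. As an illustration, suppose diameter alone explained 10% of growth variance and correlated 0.8 with baseline volume (both assumed). Volume would carry 0.8² × 0.10 = 0.064, leaving (0.10 − 0.064)/(1 − 0.064) = 0.038, about 4%. That corresponds to the 81.6% row. Centre and diabetes do not enter the model in any form.

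**Step 4: type I error of the unadjusted test.**
- With perfect balance on the factors it would be 2 × (1 − Φ(1.96/√(1 − R²))), which is 4.4%, 3.9% and 2.8% for R² of 0.05, 0.10 and 0.20. Perfect balance is not realistic with about 4 participants per stratum and blocks of up to 8, so these values overstate the conservatism.
- The stratified block scheme was therefore simulated, with a t test on growth standing in for the mixed model. Assumptions: 148 completers; block sizes 2, 4, 6 and 8 equally likely; centre shares 35/30/20/15%; 25% with diabetes; diameter bands 25/25/20/20/10%; the three factors contributing about equally. Across separate runs the type I error was about 4.8–4.9% at R² 0.05, 4.1–4.2% at 0.10 and 3.4–3.7% at 0.20.

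**The case against.** The strongest reply is that the plan is internally consistent. The sample size was computed for an unadjusted comparison, that power is delivered, the estimate is unbiased, and any error is on the safe side. The baseline constraint already takes up part of the most plausible prognostic factor, and the article says nothing about centre or diabetes affecting growth. All of this stands. It limits the point to lost precision of unknown size, and it makes the 20% case the optimistic end of an assumed range.

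Three stronger readings are tempting, and the document supports none of them.

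- **Selective adjustment of the primary result.** A reader might infer this because adjusted analyses depend on the primary results. But the primary test is tied to one named model and one contrast, and the adjusted analyses are described as additional. They are exploratory and do not replace the primary result. The allowance for adding terms to the model follows directly on the sentence about covariance fit and most naturally refers to that.
- **A biased estimate where blocks stay incomplete.** Imbalance left in one realised trial is chance imbalance, and the standard error already covers it.
- **Harm from unequal arm totals under sparse blocking.** Covariate adjustment does not change arm totals, and 79 against 69 completers still gives 79.8% power.

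It could also be said that an unseen analysis plan may add the covariates. If so, it would depart from the model published here.

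**Conclusion.** The point holds as a matter of efficiency. Randomisation is stratified on three factors and the stated primary model uses none of them; the secondary models follow the same pattern. The validity of the primary test and the claimed 80% power are not in question.

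The direction is clear wherever the factors are prognostic. The size rests on an R² that the article does not give. A gain of about 1.6 to 4 points of power follows if the factors explain 4–10% of growth variance beyond baseline volume, and about 8 points at 20%. At zero there is no gain and no material loss. The mild conservatism of the unadjusted test depends in addition on the assumed stratum frequencies and block sizes.

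**What to change.** In Data analysis, add centre, diabetes and baseline ultrasound diameter to the fixed part of the primary mixed model, each with its interaction with CT time. The interaction is needed because a main effect alone shifts both measurements equally and does not act on growth. Use main effects of the three factors, not 40 stratum cells. Make the same change in the analogous secondary models. Keep the model as now listed as a sensitivity analysis. It would help to say in one clause that the additional adjusted analyses are exploratory.

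The cost is a sentence or two of text. All three variables are already needed for randomisation, so no new data are collected. The adjustment spends 5 df on growth with diameter continuous, or 8 with diameter in bands, out of 146. Even if the factors explain nothing, the loss of power is under about 0.1 percentage point in the calculation above. The article reports that recruitment is under way, so the change should be fixed before anyone sees unblinded growth data.

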### Trial and data organisation

This project has been developed through collaboration between experts in the biology and clinical management of AAA, aortic imaging and clinical trials. The trial steering committee comprises senior vascular investigators from the centres involved and experts in drug trials and data analysis. This will be the main policy- and decision-making committee for the study and will meet by teleconference on a quarterly basis. The clinical trial randomisation centre will be located at the NHMRC Centre for Cardiovascular Research & Education in Therapeutics at Monash University. A study coordinator located at James Cook University will coordinate activities across all the participating sites, assisting with local ethics reports, and communicating with the local sites, including updates and maintenance of the trial website, central computerised randomisation, data collection, entry and processing. Trial coordination will be facilitated by a clinical trial network established by the National Health and Medical Research Council-funded Centre of Research Excellence for Peripheral Arterial Disease. To determine whether important differences in the incidence of significant AEs exist between the treatment arms, an independent safety committee has been formed. The core imaging/biomarker laboratory located in Townsville will receive DICOM images of the CT scans and frozen serum/plasma to assess the CT and biomarker outcomes. Baseline and follow-up data will be collected on CRFs. All data will be stored in a central database and examined for data quality. A publications committee will oversee the preparation of reports arising from the study.

## Discussion

One of the main risk factors for AAA is age, with the problem being much more common in the > 60-year-old age group [1, 8]. With the continued expansion in the elderly population, the number of AAA operations can be expected to continue to increase [78]. Alternative forms of treatment for AAA are urgently needed, ideally those which are non-invasive, suitable for the older age group and cost-effective. The IMAGEN trial will be the first randomised trial, to our knowledge, to assess the value of myo-inositol in limiting AAA growth. To date, only two trials of medical treatment of AAA with sufficient sample size have been published, and both had negative findings [9, 79]. If the present hypotheses are confirmed, it is estimated that myo-inositol could lead to a reduction in AAA surgery of ~ 1–2% per year at the expense of a low-cost dietary supplement. The results of this trial could markedly change the clinical management of small AAAs, which currently consists of ultrasound surveillance. This study will also provide important information on (a) biomarkers which predict responsiveness to myo-inositol, (b) the effect of myo-inositol on cardiac events and (c) biomarkers for AAA growth. The IMAGEN trial may identify circulating markers which can be used to guide management of small AAA and selection for therapy by drugs or surgical interventions.

### Trial status

Participants are currently being recruited.

## Abbreviations

AAA: Abdominal aortic aneurysm
ABI: Ankle-brachial index
AE: Adverse event
AP: Anteroposterior
BP: Blood pressure
CCL22: C-C motif chemokine 22
CRF: Case report form
CT: Computed tomography
CV: Coefficient of variation
GCP: Good clinical practice
HDL: High-density lipoprotein
IMAGEN: Inositol in the MAnaGemENt of abdominal aortic aneurysm
LDL: Low-density lipoprotein
MMP: Matrix metalloproteinase
mTOR: Mechanistic target of rapamycin
NF-κB: Nuclear factor kappa-light-chain-enhancer of activated B cells
NHMRC: National Health and Medical Research Council
OPG: Osteoprotegerin
OPN: Osteopontin
PWRI: Peak wall rupture index
PWS: Peak wall stress
SAE: Serious adverse event
SF-36: 36-item Short Form Health Survey
SOST: Sclerostin
SPIRIT: Standard Protocol Items: Recommendations for Interventional Trials
